### **10.4 Interim Analysis**

We do not plan to perform any interim analyses for efficacy. We will follow the recommendations of the external Data and Safety Monitoring Board (DSMB) to establish the specific rules for interim analyses for safety, either before commencement or very early stages of the trial. Specifically, we a priori plan to use the proportion of completed person-time of follow-up as the information statistic; test-statistic for comparison of proportions of (serious) adverse events to define the Brownian motion process; and an alpha-spending function discussed in Lan and DeMets (1983) to define a safety boundary. We will defer to the recommendation of DSMB regarding specific time points for interim safety analyses (expecting them to be approximately annually or otherwise coincide with DSMB meetings); whether the functional form of the alpha-spending function should be Pocock, O'Brien-Fleming or another function; and any other aspect of interim safety monitoring.

### **10.5 Sample Size Adequacy**

Sample size is estimated based on preliminary data from our pilot studies; our ability to detect statistical significance in two-tailed tests conducted at the  $\alpha=0.05$  level unless otherwise noted; and conservative expected dropout rates of 10, 15 and 20% during the 12-, 24- and 36-week follow-up. Thus, we conservatively anticipate 55, 52 and 49 participants to complete the 12-, 24- and 36-week assessments, respectively. We used standard sample size and power computation methods available in the literature and commercial software (PASS®; Number Cruncher Statistical Systems, Inc., Kaysville, Utah).

#### **10.5.1 Primary Outcome**

Our primary outcome on which the sample size justification is based is gait speed. Our preliminary data suggest a conservative estimate of between-subject standard deviation in baseline gait speed is 0.17 m/s and baseline to follow-up change in gait speed is 0.15 m/s. Moreover, a meaningful change in gait speed is approximately 0.10 m/s. With the proposed number of 124 in each intervention, we will have >99% power to detect statistical significance of a between-intervention difference of such magnitude in 12-

week change (primary hypothesis 1.1). We anticipate that approximately half of the participants will belong to the slower baseline gait speed stratum. Thus, with the expected number of 62 participants within each arm within each stratum, we will be able to detect statistical significance of a between-intervention difference in 12-week change within each stratum (slower/faster baseline gait speed) with 96% statistical power (hypothesis 1.2). For 24- and 36-week gait speed change, we will have 92% and 90% statistical power, respectively, within each stratum (delayed effect and sustained effect hypotheses). If the anticipated split between slower and faster walker strata turns out to be no worse than 55%-45%, we will still have  $\geq 90\%$  power for both strata for hypothesis 1.2; and if it is no worse than 67%-33%, we will still have  $\geq 80\%$ .

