## 1 STUDY OBJECTIVES

### 1.1 Primary Objective

**To determine if a standard-plus program is more successful in improving walking ability (i.e. gait speed) at 12 weeks after study entry compared to a standard exercise program.** *Compared to participants receiving the standard program, participants receiving the standard-plus program will have greater gains in gait speed at 12 weeks after study entry (Hypothesis 1.1); and differences in gains between the programs will occur in both slower ( $<1.0$  m/s) and faster ( $\geq 1.0$  m/s) walkers (Hypothesis 1.2).*

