### 10.5.2 Secondary and Tertiary Outcomes

Regarding secondary and tertiary outcomes, our preliminary data suggest conservative estimates of between-subject standard deviations in baseline measures of 0.9 s (Figure 8 time), 8.8 points (LLFDI function), 12.1 points (LLFDI disability limitation) and 53.1 m (6-minute walk test). Baseline to follow-up change standard deviations, respectively, were 1.08 s, 5.5 points, 11.8 points and 42.8 m. With the proposed sample size of 124 (and 98 anticipated completers at 36 weeks) per intervention arm, we will be able to detect statistical significance of between-intervention differences as small as 0.43 s, 2.2 points, 4.7 points and 17.2 m, respectively, with 80% power in two-tailed tests. These differences for the sustained effect hypotheses correspond to small-moderate Cohen's effect sizes of 0.25-0.48 for all secondary outcomes. Statistical power for the immediate and delayed effect hypotheses should be even greater due to greater numbers of participants in study at the earlier 12- and 24-week time points.

In summary, we have proposed an adequate sample size for successfully addressing the aims of the project, with a higher degree of statistical sensitivity reflected by  $\geq 90\%$  power for detecting meaningful differences in the primary outcome gait speed; and adequate statistical sensitivity reflected by  $\geq 80\%$  power for detecting small to moderate effects in secondary and tertiary outcomes.

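### The 96% within-stratum power for hypothesis 1.2 leaves out the plan's own 10% dropout (about 93% with it), and the chance of significance in both strata, about 87%, is not reported

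*Supplement*

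**What the plan says.** The current protocol (version 1.4) makes gait speed at 12 weeks the primary outcome. Section 1.1 places hypothesis 1.2 under the primary objective and words it so that "differences in gains between the programs will occur in both slower" and faster walkers. Section 10.1 treats the 12-week test in each stratum as a formal test of that hypothesis and gives no rule for combining the two.

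Section 10.5 bases sizing on "our ability to detect statistical significance in two-tailed tests conducted at the" 0.05 level and on dropout of 10%, 15% and 20% by weeks 12, 24 and 36. It concludes that "we conservatively anticipate 55, 52 and 49 participants to complete the 12-, 24- and 36-week assessments, respectively".

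Section 10.5.1 gives the design values: "a meaningful change in gait speed is approximately 0.10 m/s", and the standard deviation of "baseline to follow-up change in gait speed is 0.15 m/s". With an expected 62 per arm per stratum, it says a 12-week difference will be detected "within each stratum (slower/faster baseline gait speed) with 96% statistical power (hypothesis 1.2"). The next sentence gives 92% and 90% per stratum for weeks 24 and 36. The section then promises at least 90% for both strata if the slow/fast split is no worse than 55-45, and at least 80% if no worse than 67-33. Section 10.5.2 sums up with at least 90% "power for detecting meaningful differences in the primary outcome gait speed".

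**The concern.** Two things do not line up.

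First, section 10.5 says dropout is built into the sizing, yet the 12-week stratum power is tied to 62 per arm, which is the number randomised. A reader comparing 96%, 92% and 90% would take the decline as the effect of growing dropout. Part of it is a change of basis between the first figure and the other two.

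Second, hypothesis 1.2 speaks of both strata, but the plan reports power only for one stratum at a time. The chance that two independent tests both succeed is lower than the chance that either one does. The statement about a 55-45 split speaks of power for both strata, so it can be read as a joint figure. The summary in section 10.5.2 does not say which kind of power it means.

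At stake is how the stated power of a primary hypothesis is read. The sample size and the tests themselves are not affected.

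**Working it through.** **Inputs**
- Difference δ = 0.10 m/s and SD of change σ = 0.15 m/s (section 10.5.1).
- Two-sided α = 0.05 and dropout of 10/15/20% (section 10.5).
- 1:1 allocation within stratum (section 10.6).
- Randomised per arm per stratum: 248 / 4 = 62.
- Completers: 62 × 0.90 = 55.8, 62 × 0.85 = 52.7 and 62 × 0.80 = 49.6. Rounded down, these are the plan's 55, 52 and 49, so those counts are per arm per stratum.

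**Formula.** The noncentrality is δ / (σ√(2/n)). The normal approximation to power is Φ(δ / (σ√(2/n)) − 1.96). The t version uses the noncentral t distribution with 2n − 2 degrees of freedom.

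**Step 1: reproduce the plan's figures**

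| n per arm per stratum | Basis | Noncentrality | Normal | t | Plan |
|---|---|---|---|---|---|
| 62 | all randomised | 3.71 | 96.0% | 95.8% | 96% (week 12) |
| 55 | week-12 completers | 3.50 | 93.8% | 93.4% | not given |
| 52 | week-24 completers | 3.40 | 92.5% | 92.0% | 92% |
| 49 | week-36 completers | 3.30 | 91.0% | 90.4% | 90% |

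The 96% comes from 62 per arm and not from 55. The 92% and 90% come from completers, and the t version matches them to the rounded figure. On the completer basis the 12-week power is 93.4%, a drop of 95.8 − 93.4 = 2.4 points from the same calculation at 62.

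**Step 2: significance in both strata at 12 weeks.** The strata contain different people, so the two tests are treated as independent and their powers multiply.
- No dropout: 0.958² ≈ 91.7%.
- 55 completers: 0.934² ≈ 87.2% (t), or 0.938² ≈ 87.9% (normal).

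Neither dropout alone (93.4%) nor the both-strata requirement alone (91.7%) brings the figure below 90%. The two together do.

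**Step 3: unequal splits.** Completers per arm over both strata: 124 × 0.90 = 111.6.

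| Split | n per arm, larger / smaller stratum | Power (t), larger / smaller | Both (t) | Both (normal) |
|---|---|---|---|---|
| 55-45 | 61.4 / 50.2 | 95.6% / 91.1% | 87.1% | 0.9585 × 0.9163 = 87.8% |
| 67-33 | 74.8 / 36.8 | 98.2% / 80.6% | 79.1% | 0.9828 × 0.8162 = 80.2% |

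Starting instead from 2 × 55 = 110 completers per arm, the smaller stratum has 90.7% (55-45) and 80.0% (67-33), and the joint figures are 86.5% and 78.4% (t). Read per stratum, the plan's assurances of at least 90% and at least 80% therefore hold after dropout.

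**Step 4: hypothesis 1.1.** With 111 completers per arm the power is 99.9%, so the claim of more than 99% stands.

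**The case against.** The best defence is that the plan claims power within each stratum and openly ties 96% to 62 participants, for which it is arithmetically right. After dropout the per-stratum figures are 93.4%, 92.0% and 90.4%, so the summary of at least 90% is true for every gait-speed test the plan powers at an even split. That stands, and it limits the point to one figure on the wrong footing and one figure not reported.

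It can also be said that section 10.1 sets no rule requiring both tests to be significant, and that section 1.1 states where an effect is expected, not how success is decided. That is fair. The 87% is conditional on reading hypothesis 1.2 as its wording suggests.

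Thirdly, the planned model adjusts for baseline and missing data are multiply imputed, so a completers-only calculation on raw change may be pessimistic. With 55 per arm, joint power reaches 90% once the residual SD falls to about 0.145 m/s. As an illustration, assume the follow-up SD equals the baseline SD of 0.17 m/s. The correlation is then 1 − 0.15² / (2 × 0.17²) = 0.61, the residual SD is 0.17 × √(1 − 0.61²) ≈ 0.135 m/s, and joint power is about 94%. The documents give neither a baseline/follow-up correlation nor a within-stratum SD, and the plan's own figures match the unadjusted 0.15, so this remains an assumption.

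Finally, the Final Statistical analysis plan obtains stratum findings from a single model with a stratum-by-intervention term, which two separate t-tests only approximate. It restates no power, so section 10.5.1 remains the only statement on the matter.

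**Conclusion.** The 96% is not on the basis that section 10.5 sets out. With the plan's 10% dropout the 12-week power is about 93% per stratum (93.4% by t, 93.8% by the normal approximation). If hypothesis 1.2 requires significance in both strata, the chance at 12 weeks is about 87%, or about 87% with a 55-45 split and 79% with a 67-33 split, and the plan reports none of these. The figures rest on a true difference of 0.10 m/s in each stratum, an unadjusted SD of 0.15 m/s, two-sided 0.05, and analysis of completers.

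A reader might infer more than the documents support:
- **That the promised 90% is not delivered.** The promise is per stratum and survives dropout; only the joint reading falls short, by about 3 points.
- **That 79% breaks the promise of at least 80% under a 67-33 split.** That compares a joint figure with one that can be read as per-stratum, where it holds at about 80%. The joint figure itself is 79% or 80% depending on the approximation.
- **That the joint reading carries over to weeks 24 and 36.** Hypothesis 1.2 concerns week 12 only, and the delayed and sustained hypotheses do not mention both strata.
- **That a null result in one stratum is likely to be over-read because joint power is lower.** Reading such a result depends on that stratum's own power, about 93%.
- **That power should be judged at the slow-walker pilot's smaller difference.** The design difference is the meaningful change of 0.10 m/s, and section 2.4 notes that the pilot's arms differ from those of this trial.

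The point is minor.

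**What to change.** In section 10.5.1, restate the 12-week power for hypothesis 1.2 as about 93% per stratum after 10% dropout (55 completers per arm per stratum), so that it stands on the same basis as the 92% and 90%. Label the statements of at least 90% and at least 80% in section 10.5.1, and the at-least-90% gait-speed summary in section 10.5.2, as per-stratum power at a difference of 0.10 m/s. Add one sentence saying that the chance of significance in both strata at 12 weeks is about 87% on the unadjusted SD of 0.15 m/s.

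The cost is a few lines of text and one less favourable figure. The sample size, tests and analyses do not change. Since the Final Statistical analysis plan describes an analysis already carried out, the correction can be made as a clarifying note.

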### 10.5.2 Secondary and Tertiary Outcomes

Regarding secondary and tertiary outcomes, our preliminary data suggest conservative estimates of between-subject standard deviations in baseline measures of 0.9 s (Figure 8 time), 8.8 points (LLFDI function), 12.1 points (LLFDI disability limitation) and 53.1 m (6-minute walk test). Baseline to follow-up change standard deviations, respectively, were 1.08 s, 5.5 points, 11.8 points and 42.8 m. With the proposed sample size of 124 (and 98 anticipated completers at 36 weeks) per intervention arm, we will be able to detect statistical significance of between-intervention differences as small as 0.43 s, 2.2 points, 4.7 points and 17.2 m, respectively, with 80% power in two-tailed tests. These differences for the sustained effect hypotheses correspond to small-moderate Cohen's effect sizes of 0.25-0.48 for all secondary outcomes. Statistical power for the immediate and delayed effect hypotheses should be even greater due to greater numbers of participants in study at the earlier 12- and 24-week time points.

In summary, we have proposed an adequate sample size for successfully addressing the aims of the project, with a higher degree of statistical sensitivity reflected by  $\geq 90\%$  power for detecting meaningful differences in the primary outcome gait speed; and adequate statistical sensitivity reflected by  $\geq 80\%$  power for detecting small to moderate effects in secondary and tertiary outcomes.

## 10.6 Treatment Assignment Procedures - Randomization

We will use the high quality pseudo-random deviate generator available in SAS® (SAS Institute, Inc., Cary, North Carolina) to randomize participants to standard or standard-plus interventions in a 1:1 ratio, stratified by whether a slower ( $<1.0$  m/s) or faster ( $\geq 1.0$  m/s) walker at baseline. Within each baseline gait speed stratum, we will do a blocked randomization to force continued approximate balance between the numbers of subjects in each arm during recruitment. The block size will be randomly selected to be 4 or 6 to prevent personnel from predicting treatment arm. For example, if the first two participants are randomized to active interventions, the assignment of the next participant cannot with certainty be predicted to be control. The study statistician will create randomization schedules for the two strata which contains a randomization sequence number (different from a participant's study identification number) and assigned arm. Randomization sequence numbers will be readily distinguishable between the strata (ie. starting from 4001 for slower and 8001 for faster baseline walkers). Then he will pass the randomization schedules to data management personnel so that they can be incorporated into the data management system itself. At

the time of randomization, research personnel will indicate the eligible participant to be randomized in the data management system. The system will first determine the stratum of the participant being randomized, and then use the next available randomization sequence number for that particular stratum to determine the intervention assignment based on the schedule constructed by the study statistician, record the intervention assignment in a restricted location in the database inaccessible by the blinded personnel, and retire the used randomization sequence number and randomized participant number from the randomization process. Personnel assessing follow-up outcomes will be blind to intervention assignment.

## **11 DATA COLLECTION AND QUALITY ASSURANCE**

### **11.1 Data Collection Forms**

Data collection will consist of a combination of paper forms and direct data entry. Data collected on paper forms will be entered into the electronic database by the research staff. A complete set of paper forms will be available at all times to be used if the database is temporarily unavailable. Please see the Manual of Procedures for a copy of all data entry forms.

Screening and baseline data collection, which will occur prior to randomization, will be conducted by research staff trained in the outcomes and may include the study coordinator if necessary. Outcome assessments at 12, 24 and 36 weeks will only be conducted by research staff trained in the outcomes and who are blinded to the intervention group assignment.

Participants' confidentiality will be protected in the data collection process. All study personnel are certified in Research Practice Fundamentals, Human Subjects Research Module. Consent forms and paper data collection forms will be stored in locked file cabinets. All computers are password protected. The database will be web-based and accessible with a username and password. Only authorized team members will have access to personal information needed for tracking and informed consent.

### **11.2 Data Management**

The PI will oversee all aspects of data management. The Data Center (DC) will create an electronic System for Data Management (eSYSDM), based on detailed study protocols and requirements that includes an electronic case report form and a tracking system. The eSYSDM is developed using .NET 2.0 to create the interface and SQL for the database. The DC will work closely with investigative team and other study personnel to ensure that protocols are being followed, data integrity and confidentiality are maintained, and that the data contains a minimum amount of missing data. All study files residing in designated network folders will be backed-up daily and archived weekly. The weekly archived files are maintained for 1 year until the data are erased. All study subjects will be assigned unique study identifiers that will appear on all data collection instruments, tapes, documents, and files used in the statistical analysis and manuscript

preparation. Only authorized team members will have access to personal information needed for tracking and informed consent. Other data quality assurance measures will include detailed documentation of computer operations and data editing procedures and regular meetings with project staff to review any changes in procedure. The DC also has specific data quality measures that will be implemented. These include data verification, built in data validation mechanisms such as logic and out of range data checks, and repeated evaluation of the data collection and entry process.

### **11.3 Quality Assurance**

Ongoing QA monitoring will be performed by the data center, study statistician ([name]) and the study coordinator. The DC or [name] will perform exploratory statistical investigations of aggregate data to identify unusual patterns and distributions. Monthly reports will be generated showing the frequency of missing data, delinquent forms, and other study performance parameters. These reports will be reviewed by the study coordinator who will promptly initiate action to remedy any problems, and will perform follow-up evaluations of actions taken, if necessary.

A quality assurance meeting will be held with all study staff prior to the enrollment of the first subject. Additional QA meetings will be held annually during the enrollment and follow-up period. If problems are identified, the PI will develop a corrective action plan for the staff with clearly defined tasks and timelines. The PI will track the implementation of the plan and assure that all tasks are completed within the defined timeframe.

At the QA meetings, study staff will discuss any difficulties they are having and will work collectively with the study investigators to resolve the problems. Additional meetings will be held if there are concerns about data quality or protocol adherence.

The purposes of the QA meetings will be to:

- Assure the rights and safety of participants
- Assure that informed consent has been obtained and documented in accordance with the protocol and NIH regulations
- Verify adherence to the protocol and exam staff knowledge via discussions
- Discuss screenings, informed consent process, assessments and interventions and to confirm that staff are following good clinical practice
- Ensure secure maintenance of required documents
- Review participant files for completeness
- Assure that information recorded on forms is complete and accurate
- Assure accurate reporting and documentation of all AEs
- Review data quality reports

Protocol deviations will be captured on the protocol deviation form and entered into the database. Protocol deviations will reviewed and discussed at monthly team staff meetings. The study coordinator, with input from the study investigators, will promptly

initiate action to remedy any problems, and will perform follow-up evaluations of actions taken, if necessary.

## **12 PARTICIPANT RIGHTS AND CONFIDENTIALITY**

### **12.1 Institutional Review Board (IRB) Review**

The study protocol, the informed consent document and any subsequent modifications will be reviewed and approved by the University of Pittsburgh IRB.

### **12.2 Informed Consent Forms**

All potential participants will be adults (65 years of age or older) who are capable of providing direct consent for their participation in the study. Written informed consent will be obtained at the clinic screening visit prior to performing any of the clinic screening procedures. One of the study investigators will explain the study and the participant will be given a copy of the consent form to read. The consent form will describe the purpose of the study, the procedures to be followed, and the risks and benefits of participation. The investigator will answer any questions that the participant may have about the study. Finally, the participant will be asked to sign and date the consent form. The participant will be given a copy of the consent form for their records.

### **12.3 Participant Confidentiality**

Participant privacy will be protected throughout the research process. Research assessments and interventions are conducted in the PT-CTRC located in the Bridgeside Point Building at the University of Pittsburgh. This space includes several small rooms that can be used to privately conduct questionnaires and simple physical examination measures. Many of the walking assessments are done in the open area of the center, which includes the oval track, the computerized walkway system and treadmills. Participants may be screened individually, which further protects their privacy. Participants are informed via the consent process that the treatment programs may be conducted in small groups. Although not completely private, this level of exposure to others during exercise is similar to what one might experience at a physical therapy appointment or during an exercise routine at a public gym. This research will not involve the use or disclosure of existing identifiable medical information, such as personal medical or hospital records.

Participants' confidentiality will be protected in the data collection process. Consent forms and data collection forms that identify the participant by name will be stored in a locked cabinet. All computers are password protected. If the data are used in scholarly presentations or journal articles, the investigators will protect the anonymity of individual participants and will report only aggregate data (eg group means) where appropriate. The Principal Investigator will review data confidentiality processes monthly or as indicated with the project staff (Study coordinator and Physical Therapists). The Investigators are all certified in Research Practice Fundamentals, Human Subjects Research Module.

